### Method of allocation and randomization

All recruited subjects will be randomly allocated to either the flow diverter implantation group or the control group using a web-based platform linked to a central randomization database. According to existing research, aneurysms larger than 15 mm with posterior circulation are thought to carry a higher complication rate [26,27]. Stratification will be performed for aneurysm size (≦15 mm versus >15 mm) and aneurysm location (anterior circulation versus posterior circulation).

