### Sample size

The sample size calculation is based on the study of Mocco et al. [28], who reported the midterm results of 219 patients treated with Enterprise-assisted stent coiling. In their research, the 6-month complete occlusion rate was 40%; of these, 46.4% were cases of aneurisms smaller than 7 mm. Because the aneurysmal complete occlusion rate decreases with aneurysm size, we assume the 6-month complete occlusion rate to be 35% following Enterprise stent-assisted coiling for aneurysms larger than 10 mm. Furthermore, the 6-month complete occlusion rate for the Tubridge FD implantation is predicted to be 65% according to our previous results and to those of other studies using Silk or Pipeline implantation. Thus, at least 98 patients will need to be randomized in the ratio of 1:1 (49 in each group) to obtain a positive result (two-tailed test, significance level of α = 0.05, power (1 - β) = 0.80). Considering a withdrawn-patient maximum of 20%, the sample size will increase to at least 124 (62 in each group).

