### Planned analyses

Statistical analyses will be conducted based on an intention-to-treat (ITT) population. Participants who are recruited and treated will be considered the full analysis set (FAS), those who complete treatment and the entire follow-up protocol will be considered the per-protocol set (PPS), and those who are treated and have at least one safety evaluation will be considered the safety set (SS). Last observation carried forward (LOCF) method will be implemented to handle the missing data from withdrawn subjects, who would be included in FAS.

Comparisons of demographic information will first be conducted to measure the balance between the two groups. Then evaluation of primary and secondary outcome will conducted as below:

Primary outcomes:

The comparison of the treatment groups with regard to the primary endpoint will be performed with the data of the Full Analysis Set as well as of the Per Protocol Set. In case the two analyses will lead to different conclusions the result of the analysis of the Per Protocol Set is deciding.

Use superiority test for analysis of primary outcome. The formal test problem is as follows:

Test problem for the complete occlusion rate at 6-month follow-up:

Let πT be the rate of complete occlusion rate of treatment group at 6-month follow-up.

Let πc be the rate of complete occlusion rate of control group at 6-month follow-up.

The superiority margin δ is 0.

Test problem:

H0: πT -πc ≥ 0

H1: πT -πc < 0

α = 0.05 (2-sided)

The alternative hypothesis will not be accepted unless the lower limit of the 95% confidence interval of the difference of occlusion rate lies above the superiority margin.

Secondary outcomes:

Immediate occlusion rate will be conducted in FAS group, while other safety evaluation will be be conducted in SS group. For quantitative data, t-test (for equal variances and normal distribution) or Wilcoxon rank sum test could be applied according to the distribution of the data. The categorical variables will be compared between study arms using Chi-square tests or Fisher's exact tests (if Chi-square test is not valid). Besides, for immediate technique success rate, 95% confidence interval of each groups and difference between groups will be estimated.

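### Randomisation is stratified by aneurysm size and location, but the written comparisons name no stratum; if the strata are prognostic, the primary interval is somewhat too wide (conservative)

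*Protocol article*

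**What the plan says.** **Allocation.** Under Method of allocation and randomization: "Stratification will be performed for aneurysm size (≦15 mm versus >15 mm) and aneurysm location (anterior circulation versus posterior circulation". The reason given concerns complications: "aneurysms larger than 15 mm with posterior circulation are thought to carry a higher complication rate".

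**Prognosis.** Sample size links size to the primary endpoint: "Because the aneurysmal complete occlusion rate decreases with aneurysm size". On that ground it lowers the reported control rate from 40% to 35%. It gives no rates either side of the 15 mm cut, and nowhere ties location to occlusion.

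**Primary analysis.** Planned analyses says "Use superiority test for analysis of primary outcome". It defines πT and πc as the occlusion rates of the two whole arms, sets the margin at 0, and decides on the lower 95% limit of their difference. No stratum, weight, covariate or interval method is named.

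**Other endpoints.** Under secondary outcomes: "The categorical variables will be compared between study arms using Chi-square tests", with Fisher's exact test as the fallback.

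**The concern.** When allocation is balanced within strata that predict the outcome, part of the outcome variation is shared equally by the arms and cannot contribute to their difference. The usual two-proportion variance still counts it. The interval is then wider than it need be, and the test rejects a true null less often than its nominal level.

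The protocol treats size as prognostic for occlusion and stratifies on it, but the comparison as written does not use it. For the complication endpoints the mismatch is more explicit: complications are the stated reason for stratifying, and the tests named are unstratified. What is at stake is some precision already bought at randomisation.

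**Working it through.** **1. The plan's own figure.** Inputs from Sample size: "we assume the 6-month complete occlusion rate to be 35% following Enterprise stent-assisted coiling for aneurysms larger than 10 mm" and "the 6-month complete occlusion rate for the Tubridge FD implantation is predicted to be 65"%; two-sided α 0.05; power 0.80; 20% withdrawal.

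- Without continuity correction: n = [1.96·√(2·0.5·0.5) + 0.8416·√(0.35·0.65 + 0.65·0.35)]² / 0.30² = 42.4, so 43 per arm.
- With continuity correction: (42.4/4)·[1 + √(1 + 4/(42.4·0.30))]² = 48.8, so 49 per arm, as stated.
- 49/0.80 = 61.25, so 62 per arm and 124 in total, as stated.

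**2. Large-sample size of the effect.** Assumptions, because the documents give no stratum rates: two equal strata, balanced arms, and the same gap g between strata in both arms.

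- Unstratified variance × n: 0.35·0.65 + 0.65·0.35 = 0.455.
- Within-stratum variance × n: 0.455 − 2·(0.5·0.5)·g² = 0.455 − g²/2.
- Ratio of standard errors, stratified to unstratified: √[(0.455 − g²/2)/0.455].
- Unstratified half-width at 62 per arm: 1.96·√(0.455/62) = 16.8 points.

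| Gap g | Ratio | Stratified half-width (points) | Excess width of unstratified (1/ratio − 1) |
|---|---|---|---|
| 5 points | 0.9986 | 16.8 | 0.1% |
| 10 | 0.9945 | 16.7 | 0.6% |
| 20 | 0.9778 | 16.4 | 2.3% |
| 30 | 0.9493 | 15.9 | 5.3% |
| 40 | 0.9078 | 15.2 | 10.2% |

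An 85/15 split shrinks the effect: at 20 points the ratio is √[(0.455 − 2·0.85·0.15·0.04)/0.455] = 0.989.

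**3. Finite samples, two equal strata** (200,000 simulated trials, 62 per arm). For gaps of 10, 20, 30 and 40 points:

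- Coverage of the unstratified interval at 35% v 65%: 95.2%, 95.6%, 96.1% and 97.0%.
- Upper-tail error with both arms at 35%: 2.5%, 2.4%, 2.1% and 1.6%, against a nominal 2.5%.
- Power at 35% v 65%, unstratified v stratified: 94.0% v 94.0% at a 20-point gap and 94.4% v 94.9% at 30.

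**4. Finite samples, four strata.** Assumed 28/22/7/5 patients per arm, in the order anterior ≤15 mm, anterior >15 mm, posterior ≤15 mm, posterior >15 mm; 200,000 trials, except that the 45-point SD is from 40,000. The stratified analysis is the Mantel-Haenszel risk difference with the Sato variance. With equal arms in each stratum its point estimate equals the crude difference, so only the standard error changes.

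| Assumed control rates | Mean unstratified SE v true SD (20-point effect) | One-sided error, unstratified | Power at 30-point effect, unstratified v stratified |
|---|---|---|---|
| 37/32/37/32% (5-point gap) | 0.0868 v 0.0874: no excess | 2.7% | 93.5% v 93.5% |
| 45/25/40/20% (20-point gap) | 0.0869 v 0.0857: 1.4% too wide | 2.3% | 94.0% v 94.1% |
| 60/15/55/10% (45-point gap) | 0.0874 v 0.0786: 11% too wide | 1.5% | 95.8% v 97.7% |

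The 2.7% in the first row reflects the simple large-sample interval at this sample size, not the omission of strata. In that row the Cochran-Mantel-Haenszel test has slightly lower power, 92.9%.

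Across these scenarios the Sato interval covers about 94.5% to 95.0%, with one-sided error about 2.7%. A plug-in stratified variance does worse: coverage 93.6% to 94.3%, one-sided error about 3.0%, because the posterior strata hold only 5 to 7 patients per arm.

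**The case against.** The strongest reply is that this rests partly on silence. Planned analyses fixes a decision rule, not an interval method, and a Mantel-Haenszel difference would satisfy its wording. The Chi-square and Fisher sentence stands under secondary outcomes, so it does not establish the primary test. The source is a journal article, and an analysis plan that is not shown may already stratify. This stands, and it limits confidence. A reader might infer that the plan rules out a stratified primary analysis; the text does not go that far.

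A reader might also infer a material loss of power. The 45-point scenario with a 20-point treatment effect does give 65% unstratified against 73% stratified. But the documents support neither figure. The planned effect is 30 points. The only size-related shift they quantify is 40% to 35%, which is 5 points. The assumed control rates average (28·0.60 + 22·0.15 + 7·0.55 + 5·0.10)/62 = 39.4%, not 35%.

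It is also fair that location is linked only to complications, so only size has documentary support as a predictor of occlusion, and then without reference to the 15 mm cut. Finally, a carelessly chosen stratified variance can undercover in small strata. That is a reason to name the variance, not to drop stratification.

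**Conclusion.** The point holds in a limited form. The design stratifies, the protocol calls size prognostic for occlusion, and the comparison as written uses no stratum. If the eventual interval is unstratified and the strata matter, it errs on the conservative side. The crude difference is unbiased in the patients as randomised, and leaving out the strata does not inflate type I error.

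The excess width is nil at a 5-point gap between size strata, about 1 to 2% at 20 points and about 11% at 45. At the planned effect with 62 per arm, power moves by 0 to 2 points and stays well above the 80% target. All of this depends on assumed stratum shares and rates.

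Severity is minor. Confidence is moderate, because the interval method is not named and the analysis plan is not shown.

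**What to change.** In Planned analyses, before outcomes are seen:

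- Make the primary estimate the Mantel-Haenszel risk difference over the randomisation strata, with a 95% interval from a variance valid for sparse data, for example Sato's. Keep the existing decision rule on its lower limit.
- State a pooling rule: if a posterior stratum is too small, pool over location and keep size.
- Use the Cochran-Mantel-Haenszel test for the other between-arm binary endpoints where counts allow.
- Show the crude difference as supportive.

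The cost is a few lines of text and programming, with no new data or patients. The downside is almost no gain if the strata are only weakly prognostic, and coverage slightly below 95% (about 94.5%) when strata are small. If the analysis plan already specifies a stratified interval, a sentence saying so is enough for the primary comparison.

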### Sample size

The sample size calculation is based on the study of Mocco et al. [28], who reported the midterm results of 219 patients treated with Enterprise-assisted stent coiling. In their research, the 6-month complete occlusion rate was 40%; of these, 46.4% were cases of aneurisms smaller than 7 mm. Because the aneurysmal complete occlusion rate decreases with aneurysm size, we assume the 6-month complete occlusion rate to be 35% following Enterprise stent-assisted coiling for aneurysms larger than 10 mm. Furthermore, the 6-month complete occlusion rate for the Tubridge FD implantation is predicted to be 65% according to our previous results and to those of other studies using Silk or Pipeline implantation. Thus, at least 98 patients will need to be randomized in the ratio of 1:1 (49 in each group) to obtain a positive result (two-tailed test, significance level of α = 0.05, power (1 - β) = 0.80). Considering a withdrawn-patient maximum of 20%, the sample size will increase to at least 124 (62 in each group).

### Procedure

For all recruited patients, dual antiplatelet drugs (300 mg/day aspirin plus 75 mg/day clopidogrel) will be given for at least 3 days before the procedure. All procedures will be performed under general anesthesia and via the transfemoral approach. After sheath placement, heparin will be given to maintain the activated clotting time at 2 to 3 times the baseline throughout the procedure. Next, a proper (7 F) guiding catheter will be placed in the distal internal carotid artery or vertebral artery. Subsequently, the aneurysms will be treated with conventional stent-assisted coiling or FD implantation with or without coiling. All detailed data, such as the aneurysm’s actual size, width of the aneurysmal neck, aneurysmal shape, diameter of the parent artery, and treatment results, will be recorded. The post-operative antiplatelet regimen will be administered as follows: <6 w: 300 mg aspirin + 75 mg clopidogrel; 6 w-3 m: 100 mg aspirin + 75 mg clopidogrel; ≥3 m: 100 mg aspirin indefinitely.

### Planned patient follow-up

Arrangements will be made for all patients to be evaluated at discharge and 30 d (±7 d), 90 d (±15 d), and 1 year (±30 d) post-treatment, either by clinic or telephone contact. Postoperative DSA follow-up is required after 6 m (±30 d).

### Safety and efficacy assessment

During the procedure and at each follow-up time point, information about the patients will be documented in detail. All data will be collected and analyzed by an independent central laboratory to compare the complication rate, morbidity, mortality, as well as initial and follow-up angiographic results between the two groups. If any adverse event has occurred, the detailed symptoms, duration, severity, possible reasons, actions taken, results and other relevant information will be reported. In addition, researchers must fill out a serious adverse event (SAE) form and notify the principal investigator, institutional review board (IRB), China Food and Drug Administration (CFDA), Clinical Research Associate (CRA), and other regulatory authorities within 24 hours.

Immediate angiographic results will be classified according to Raymond’s classification for those treated with stent-assisted coiling or FD implantation combined with coils [29]. For aneurysms treated with the Tubridge FD alone, flow modifications will be defined as disrupted inflow jet, slow flow (if the contrast circulation within the aneurysm is slowed), or reduced contrast filling (if increased contrast stagnation is observed within the aneurysm at the late venous phase of the angiographic series) [30].

The angiographic results will be classified into four categories when compared with the immediate degree of embolization: 1) Occluded, defined as no contrast filling into the aneurysm sac; 2) Improved, defined as decreased contrast filling into the aneurysm sac; 3) Stable, defined as unchanged contrast filling into the aneurysm sac; 4) Recanalized, defined as increased contrast filling into the aneurysm sac. The intra-stent stenosis will also be documented.

Table 1 shows a summary of the intervention and follow up.

**Table 1 T1:** Summary of measurement items and point of data capture

**Point of data capture**	**Pre-procedure**	**During procedure**	**Post-procedure**					
			**24 hours**	**Discharge**	**30 days**	**90 days**	**6 months**	**1 year**
Window phase					±7 d	±15 d	±30 d	±30 d
Informed consent form	√							
Inclusion/exclusion criteria	√							
Withdrawal criteria		√			√	√	√	√
Medical history/demographic information	√							
Physical examination (1)	√			√			√	
Vital signs (2)	√	√		√				
Routine urine and blood test	√			√				
Blood biochemistry test (3)	√			√				
Blood lipid test (4)	√							
Pregnancy tests (5)	√						√	
CTA, MRA or DSA	√							
Clinical evaluation		√			√	√	√	√
DSA examination (6)		√					√	
Adverse events		√	√	√	√	√	√	√

1. Physical examination: height, weight, and neurological presentation.

2. Vital signs: systolic pressure, diastolic pressure and heart rate.

3. Blood biochemistry tests: fasting blood glucose, blood urea nitrogen, TBIL, and serum creatine.

4. Blood lipid tests: total cholesterol, triglycerides, and low density lipoprotein.

5. Pregnancy tests: restricted to women with suspected pregnancy.

6. DSA examination: angiographic images will be sent to an independent laboratory for data analysis.

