### Hypothesis

Compared with conventional stent-assisted coiling, Tubridge FD implantation does not enhance the risk of procedure-related complications and may lead to a higher complete occlusion rate and a decreased recanalization rate.

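### Recanalization is measured from an immediate image on which diverter-alone and coiled sacs start from different places, so the hypothesised reduction is biased toward the diverter by an amount the protocol does not fix

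*Protocol article*

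**What the plan says.** Four parts of the protocol article bear on this.

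- **Immediate result (Safety and efficacy assessment).** Two scales are used. For coiled aneurysms: "Immediate angiographic results will be classified according to Raymond’s classification for those treated with stent-assisted coiling or FD implantation combined with coils". For the rest: "For aneurysms treated with the Tubridge FD alone, flow modifications will be defined as disrupted inflow jet, slow flow", or reduced contrast filling. None of these three descriptors is an occlusion grade. Under Study design, a diverter without coils is possible only in the treatment group.
- **Follow-up result (same section).** One scale serves both arms: "The angiographic results will be classified into four categories when compared with the immediate degree of embolization". Its first category is absolute: "1) Occluded, defined as no contrast filling into the aneurysm sac". Improved, Stable and Recanalized are changes from the immediate result; the last is "4) Recanalized, defined as increased contrast filling into the aneurysm sac".
- **Hypothesis.** Diverter treatment "may lead to a higher complete occlusion rate and a decreased recanalization rate".
- **Endpoints and analyses.** The primary endpoint is complete occlusion at 6 months. The six secondary endpoints include immediate technique success, but neither recanalization nor immediate occlusion. Planned analyses nevertheless states: "Immediate occlusion rate will be conducted in FAS group".

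**The concern.** A category defined as an increase depends on where each sac starts. A coiled sac that was closed at the end of the procedure and reopens is recorded as Recanalized. A diverter-alone sac still filling at the end of the procedure, and filling to the same extent at 6 months as that reopened coiled sac, may be recorded as Stable or Improved. Two arms with the same number of open aneurysms at 6 months could therefore report different recanalization rates, with the difference favouring the diverter. The protocol names "a decreased recanalization rate" as one of the benefits it expects, so this comparison will be read as evidence of efficacy.

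A second problem has the same source. An immediate occlusion rate cannot be computed on one scale for the whole treatment arm when the diverter-alone cases have no occlusion grade. The endpoint list also does not contain that rate.

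**Working it through.** **1. The plan's own figure, for the sample sizes used below.** Rates are 35% and 65%, two-sided α = 0.05, power 80%.

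- Uncorrected: n = [1.960·√(2·0.5·0.5) + 0.842·√(0.35·0.65 + 0.65·0.35)]² / 0.30² = 42.4, so 43 per arm.
- With continuity correction: (42.4/4)·[1 + √(1 + 4/(42.4·0.30))]² = 48.9, so 49 per arm (98 in all).
- With 20% withdrawal: 49/0.80 = 61.25, so 62 per arm (124 in all).

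The stated 98 and 124 are reproduced. The plan gives no figure for recanalization, so there is none to reproduce on that point.

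**2. The definitions side by side.**

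| Treatment given | Arm | Immediate scale | Starting point for an increase in filling |
|---|---|---|---|
| Stent-assisted coiling | Control | Raymond | Occlusion grade |
| Diverter with coils | Treatment | Raymond | Occlusion grade |
| Diverter alone | Treatment | Flow descriptors | Altered flow, no occlusion grade |

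The split is by coil use. It becomes a difference between arms only because the third row occurs in one arm.

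**3. Size of the built-in difference.**

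Inputs:
- r, the true recanalization risk of a coiled sac: 19.2% to 50%, the range that the Discussion gives for reconstructive approaches such as stent-assisted coiling.
- f, the share of the treatment arm given the diverter alone: not stated, so varied from 0 to 1.

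Assumptions: all coiled sacs in both arms have the same r, and no diverter-alone sac can be recorded as recanalized. The second is a limiting assumption.

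Recorded treatment-arm rate = (1 − f)·r. Built-in difference = r − (1 − f)·r = f·r.

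The last two columns give the exact probability that Fisher's two-sided test at 0.05, with 49 per arm, shows a significantly lower rate in the treatment arm.

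| f | Treatment-arm rate, r = 19.2% | Treatment-arm rate, r = 50% | P(significant), r = 19.2% | P(significant), r = 50% |
|---|---|---|---|---|
| 0.25 | 14.4% | 37.5% | 5% | 19% |
| 0.50 | 9.6% | 25.0% | 18% | 66% |
| 0.75 | 4.8% | 12.5% | 47% | 98% |
| 1.00 | 0% | 0% | 93% | 100% |

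At f = 0 the built-in difference is zero.

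**4. The same as single tables with 62 per arm.** 0.192 × 62 = 11.9, so 12 control events. Fisher's two-sided p is 0.63 against 9 of 62 (f about 0.25), 0.20 against 6 of 62 (f about 0.5) and 0.00027 against 0 of 62 (f = 1). Only the last assumes that nobody in the treatment arm receives coils.

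**5. Immediate occlusion.** Under Planned analyses the rate is assigned to the FAS, which includes diverter-alone patients. Those patients have no grade from which to derive it. The endpoint list has immediate technique success in its place, and the same paragraph of Planned analyses treats technique success separately. The two sections do not match.

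**6. Overlap of categories.** A sac with no filling at either time meets the definitions of both Occluded and Stable. The article states no order of precedence.

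**The case against.** The case against has several good parts.

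- **Grading does not differ by device.** A diverter with coils is graded like a control, and the four follow-up categories are the same in both arms. This stands. Only the baseline differs, and only for diverter-alone cases.
- **The size is unknown.** It rests on f, which the article does not give. This stands, and is why only a range can be reported.
- **A diverter-alone sac can in principle fill more later, and an incompletely coiled control sac also starts with residual filling.** This stands as far as it goes: the contrast is one of degree, and f × r is a limiting value. It does not remove the direction of the bias.
- **The background data prove little.** In the earlier Tubridge series 7 of 25 followed aneurysms (28%) were not occluded, 6 being improved and 1 unchanged, and none was reported as recanalized. That fits the artefact, but it fits a true device effect equally well; the article gives neither the coil mix nor the categories used. The definitions and follow-up times behind 19.2% to 50% are also not given.
- **Recanalization is not a listed endpoint and no test is specified for it.** This stands and limits the consequence. The comparison is still a stated hypothesis, and the assessment section says follow-up angiographic results will be compared between the groups.
- **Immediate occlusion may be loose wording for technique success, and precedence of Occluded is the natural reading.** Both are plausible. Either way one sentence settles the matter.

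**Conclusion.** The point holds in a limited form. As defined, the recanalization comparison is biased toward the diverter whenever part of the treatment arm is treated without coils. Under the two assumptions above the bias is f × r: nil at f = 0, and at most the whole control rate (19.2 to 50 percentage points) at f = 1. The immediate occlusion rate has no defined grade for diverter-alone cases and does not match the endpoint list.

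Two stronger readings are tempting. A reader might infer that the lower recanalization rate is largely guaranteed by definition, for instance 0 of 62 against 12 of 62. That needs every treated patient to receive the diverter alone, which the article does not say; at f = 0.25 and r = 19.2% the artefact alone would reach significance only about 5% of the time. A reader might also infer that the primary endpoint is compromised. It is not, on observed 6-month images, because Occluded is absolute and applies equally in both arms. How LOCF would treat a missing 6-month image is a separate question.

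The plan should be changed, but the effect is on a secondary claim and not on the trial's main conclusion.

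**What to change.** - Compare the arms at 6 months on one absolute, graded measure of residual sac filling, in all randomised and treated patients. It needs more than two grades: a filling/no-filling split would only be the complement of the primary endpoint.
- State that Occluded, as now defined, takes precedence over the three change categories. Leave the primary endpoint unchanged.
- Put this measure in the hypothesis in place of the lower recanalization rate. Report recanalization descriptively only, by coil use.
- Drop the between-arm comparison of immediate occlusion, and reconcile Planned analyses with the immediate technique success endpoint.
- Do not restrict the between-arm recanalization comparison to sacs closed on the immediate image. Closure at that moment is a result of the treatment received, so the restriction would break the randomised comparison and could remove most diverter-alone patients.

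The cost is small: one favourable claim is given up, and the same images need some re-reading or re-coding by the same central laboratory. No new visits or imaging are needed.

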### Participants

#### *Inclusion criteria*

Patients eligible for inclusion will meet the following criteria:

1. Age 18 years to 75 years, male or nonpregnant female.

2. Unruptured internal carotid artery or vertebral artery saccular aneurysm (including recanalized aneurysms), confirmed by CTA, MRA, or DSA.

3. Width of aneurysm neck ≥4 mm, and aneurysm size ≥10 mm.

4. Parent vessel with a diameter range of 2.0-6.5 mm.

5. Indications for Enterprise stent-assisted coiling and Tubridge FD implantation with or without coiling.

6. Is willing to return to the investigational site for follow-up according to our protocol.

7. Understands the nature of the procedure and provision of written informed consent.

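### Table 1 limits pregnancy testing to suspected cases, so for other women who could be pregnant the nonpregnancy entry criterion rests on history alone

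*Protocol article*

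**What the plan says.** The first inclusion criterion reads "Age 18 years to 75 years, male or nonpregnant female". Nothing in it limits entry by menopausal status or sterility, so it admits women who could become pregnant.

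Table 1 (Safety and efficacy assessment) has a pregnancy test row, ticked in the pre-procedure column and again at 6 months. Footnote 5 governs the whole row: "Pregnancy tests: restricted to women with suspected pregnancy".

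The Procedure section sets out what every participant then receives. On drugs: "For all recruited patients, dual antiplatelet drugs (300 mg/day aspirin plus 75 mg/day clopidogrel) will be given for at least 3 days before the procedure". On the intervention: "All procedures will be performed under general anesthesia and via the transfemoral approach". Heparin is given during the procedure and antiplatelet treatment continues afterwards. Table 1 marks digital subtraction angiography (DSA) during the procedure, and Planned patient follow-up requires it again at about 6 months.

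**The concern.** The criterion and the rule meant to check it do not match. The criterion applies to every woman who enters. The test applies only to women in whom someone already suspects pregnancy. An early pregnancy without symptoms is the case that a test would find and that suspicion would miss, and footnote 5 leaves that case untested.

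What is at stake is participant safety. By making nonpregnancy an entry condition, the trial itself treats enrolment of a pregnant woman as something to be avoided. A woman whose pregnancy goes unnoticed would pass the eligibility check and then receive the drugs, anaesthesia and X-ray angiography set for all participants. The 6-month test has a different role. It cannot serve the entry criterion, but it falls at the visit with the second required DSA, and the same restriction applies to it.

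**Working it through.** No figure in the plan depends on this point, so the check is mainly a reading of the relevant passages together. The plan's sample size is reproduced first, because it bounds any effect on the primary analysis.

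**Sample size**

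Inputs from Sample size: occlusion rates of 0.35 and 0.65, two-sided α = 0.05, power 0.80, 1:1 allocation, 20% withdrawal.

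- Uncorrected, pooled variance under the null: n = [1.96·√(2·0.5·0.5) + 0.8416·√(0.35·0.65 + 0.65·0.35)]² / 0.30² = (1.386 + 0.568)² / 0.09 ≈ 42.4, so 43 per group.
- With continuity correction: (42.4/4)·[1 + √(1 + 4/(42.4·0.30))]² ≈ 48.9, so 49 per group and 98 in total, as stated.
- With withdrawal: 49/0.80 = 61.25, so 62 per group and 124 in total, as stated.
- Allowance: 124 − 98 = 26 patients. One patient without a 6-month DSA is 1/124 = 0.8% of those randomised.

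**Who is checked, and by what**

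| Place in the protocol article | What it contributes |
|---|---|
| Inclusion criterion 1 | Nonpregnancy required of every woman; no method of verification given |
| Table 1, pregnancy test row | Test before the procedure and at 6 months |
| Table 1, footnote 5 | Both tests only where pregnancy is suspected |
| Table 1, medical history and eligibility rows | Pre-procedure history and criteria check, which may raise suspicion |
| Exclusion criteria | Pregnancy not mentioned |
| Withdrawal criteria | Pregnancy not mentioned |
| Table 1, footnotes 3 and 4 | Itemised biochemistry and lipids; no pregnancy assay |
| Table 1, routine urine and blood test | Contents not itemised; no pregnancy assay named |
| Anywhere | No contraception requirement |

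The women then fall into three groups.

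1. Those who cannot be pregnant: no test is needed, and there is no gap.
2. Those suspected of being pregnant: footnote 5 has them tested, and there is no gap.
3. Those who could be pregnant but are not suspected: footnote 5 leaves them untested, and criterion 1 rests on history.

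The gap is the third group only.

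**Timing**

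Table 1 places the first test before the procedure and does not tie it to randomisation or to confirmation of eligibility. The antiplatelet drugs start at least 3 days before the procedure. Even a woman who is tested could therefore have her result after she has been recruited and has started treatment.

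**The case against.** The strongest reply is that nothing here is contradictory. Criterion 1 does not say how nonpregnancy is to be verified, and history followed by a targeted test is a check, if a weaker one than testing every woman who could be pregnant. This stands in part. It would be wrong to infer that the criterion goes unchecked: history is taken and suspected cases are tested. It does not answer the point for unsuspected pregnancy, where the written rule gives the criterion no objective support.

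A second reply is that this is a condensed article in imperfect English. On that view, suspected pregnancy may loosely mean any woman who could be pregnant, or the routine urine test may include a pregnancy assay. Neither reading has support in the text. The article does not leave the testing rule out: it states one, and that rule narrows testing.

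Two stronger readings are tempting, and the document supports neither.

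- **A count of those affected.** If one assumes 50% to 70% women and 15% to 30% of those of childbearing potential, the arithmetic gives 124 × 0.50 × 0.15 ≈ 9 to 124 × 0.70 × 0.30 ≈ 26. Both shares are assumptions with no source in the document. The result also counts women who might go untested, not pregnancies, and it supposes that none of them would be tested as suspected.
- **Damage to the primary endpoint.** A pregnancy found after entry might lead to withdrawal or a missed 6-month DSA, and hence to a carried-forward value in the full analysis set and absence from the per-protocol set. For one or two patients this lies well inside the allowance of 26 and does not threaten the trial's result.

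**Conclusion.** The point holds as a flaw in eligibility checking and participant safety. The stated testing rule is narrower than the criterion it serves, and no other passage makes up the difference for women whose pregnancy is unsuspected.

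Its size is small in numbers. Cases would be few, and the document does not allow them to be counted. The sample size stands, and the primary analysis is not materially affected. The conclusion rests on reading footnote 5 as written and on the absence of any pregnancy check elsewhere in the article. If the full protocol, which is not shown, already tests more widely, the article's footnote misreports it and still needs correcting. This is a cheap improvement, worth making because the possible harm is avoidable.

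**What to change.** Reconcile footnote 5 with inclusion criterion 1: let the two tests already scheduled in Table 1 cover all women of childbearing potential rather than suspected cases only, and state that the pre-procedure result is to be available when eligibility is confirmed. No new visit or time point is needed.

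The cost is a one-line amendment and the small expense of a routine test in a minority of patients. The sample size, randomisation and analysis stay as they are.
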